### Aim of the study

The aim of the present project is to evaluate the performance of the first certified regional trauma network in Germany, the Trauma Network Eastern Bavaria (TNO). In order to assess *qual*it*y* of care for *poly*trauma (*POLYQUALY*) the following specific research questions will be addressed:Do standard and maximum care facilities produce comparable (risk-adjusted) levels of patient outcome?Does network formation like the TNO outperform reference data provided by the German Trauma Register DGU^®^ 2008?Does TNO comply with selected benchmarks derived from the S3 practice guideline?What barriers and facilitators in the process of delivering health care to major trauma patients can be identified? How can these factors explain the results in patient outcome?

We hypothesize that the quality of care and therefore the outcome will be equal in hospitals with standard care in comparison to hospitals with maximum care facilities in a region if all hospitals are organized into a network structure that allows mutual support including the use of latest technologies such as telemedicine consultation. Furthermore, we hypothesize that TNO outperforms German Trauma Register DGU^®^ 2008 reference data and that the quality of care in the standard and maximum care facilities of TNO complies with guideline-derived benchmarks. In case our hypotheses hold true the qualitative barriers and facilitators analysis will be able to explain what the driving forces were that made this favorable results possible. In case the study results contradict our hypotheses the barriers and facilitators analysis can explain the hindering forces and may show ways how to improve the health care situation in the region.

The present project will also consider gender aspects. The majority of trauma patients (about 70 %) are male. In this study males and females will be enrolled according to the actual incidence of trauma events. After major trauma, quality of life differs between genders. Women have a 2.5 fold greater risk than men for developing psychological problems following major trauma and intensive care treatment (post-traumatic stress disorder, PTSD) [18, 19]. In order to address these gender-specific differences, quality of life outcomes will be compared between males and females.

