### Data collection

Clinical information will be collected using the TraumaRegister^QM^ form. This quality management (QM) form underwent a rigorous development process and has been issued by the German Trauma Society. TraumaRegister^QM^ is a one-page, 40-item short form that includes among other things the following contents: date and site of referral, type of trauma, pre-hospital management, Glasgow Coma Scale (GCS), in-hospital management, ICU management and outcome at discharge (Glasgow Outcome Scale, GOS). A number of validated scores can be delineated from this documentation, such as AIS, ISS, TRISS, RISC, [20] for evaluation of adjusted outcome. TraumaRegister^QM^ will be completed by the participating hospitals via a web-based system. Data will be transferred to AUC (Akademie der Unfallchirurgie) and from there to the Centre for Clinical Studies Regensburg.

Another data source which will be used as a historical control is the German Trauma Register DGU^®^ reference data base. Quality of life will be assessed using the EQ-5D form which is a short form widely used in large scale cohort studies. This instrument underwent rigorous psychometric testing, is part of the trauma-specific QL measurement system POLO-Chart [21] and generates indices that can be used for further socio-economic analyses. A German version and population-based German reference data are available. EQ-5D assessment will be performed 6, 12 and 24 months after trauma (Fig. 2). Assignment to the respective clinical information documented in TraumaRegister^QM^ will be accomplished via an index number.

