### Biostatistical concept / statistical analysis

*Prospective cohort study*: Statistical analyses of the prospective data will primarily dwell on descriptive statistics using counts, percentages, means/standard deviations, medians/interquartiles/ranges and confidence intervals. In order to interpret descriptive results they will be compared with secondary data from the Trauma Register DGU^®^ reference data bank 2008 and the benchmarks derived from the S3 guideline on major trauma. A logistic regression will be performed with 30 day mortality as the dependent variable and the ISS and TRISS scores as covariates. A p value of < 0.05 will be considered statistically significant. All other statistical tests will be chosen according to the scale level of the variable and the number of variables used in the model (t-test, Mann–Whitney U-Test, chi-squared test, risk-adjusted multivariable regression models) and will be performed in an explanatory manner, leaving alpha at < 0.05.

*Qualitative study*: Interview and focus group transcripts will be critically examined using thematic content analysis [23]. Themes will be identified using a grounded conceptualisation process [24]. Transcripts will be repeatedly read before and after coding to ensure proper categorisation of data. For the blueprint, the information on the health care process will be visualized as a two-dimensional picture: The horizontal axis represents the chronology of actions by the patient and the health care professional. The vertical axis distinguishes between different areas of actions, i.e. direct interactions between patient and professional, professional actions visible and invisible to the patient, support processes, and planning, managing and controlling activities [15, 17].

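### The one specified mortality model does not name level of care, and other comparisons may be unadjusted, so the risk-adjusted standard-versus-maximum contrast is not secured

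*Protocol article*

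**What the plan says.** In the protocol article, Aim of the study, the first research question reads: "Do standard and maximum care facilities produce comparable (risk-adjusted) levels of patient outcome". The matching hypothesis is that "the outcome will be equal in hospitals with standard care in comparison to hospitals with maximum care facilities", given a network structure. Study design sets out the same contrast as element (a), maximum-care patients against standard-care patients.

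Biostatistical concept / statistical analysis opens by saying that "Statistical analyses of the prospective data will primarily dwell on descriptive statistics". It then gives one model with a stated outcome and stated covariates: "A logistic regression will be performed with 30 day mortality as the dependent variable and the ISS and TRISS scores as covariates". The next sentence sets the threshold: "A p value of < 0.05 will be considered statistically significant". All remaining tests are to be picked by the scale level of the variable and the number of variables. The examples run from the t-test, Mann–Whitney and chi-squared tests to "risk-adjusted multivariable regression models". These "will be performed in an explanatory manner, leaving alpha at < 0.05"; the intended word is probably exploratory.

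Data collection says of the registry form: "A number of validated scores can be delineated from this documentation, such as AIS, ISS, TRISS, RISC". It gives their purpose as the evaluation of adjusted outcome.

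**The concern.** A risk-adjusted comparison of two cohorts needs two things in the model: the cohort and the risk. The only model the article spells out names the risk and not the cohort. Its p value, taken literally, would show whether severity scores predict death, which is not one of the study questions.

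The other analyses do not close the gap. The rule for choosing them looks at the type of variable, not at whether the comparison is confounded, so an analyst could follow the plan exactly and compare mortality, ventilator-free days or EQ-5D between cohorts without adjustment.

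That matters because patients are not spread over hospitals at random. Background, Current state of research, describes routing by transport time and availability, first stabilisation in basic facilities where necessary, and onward transfer to a higher level. Quality assurance and safety provides for matching the forms of transferred patients. Case mix may therefore differ between the cohorts. At stake is whether the answer to the first research question reflects care or patient mix.

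**Working it through.** The documents give no figure that this point disputes. The first three steps are textual. The numbers after them are illustrations on stated assumptions.

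**1. What the stated model estimates.** Write L = 1 for maximum care and 0 for standard care.

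- As written: logit P(death by day 30) = b0 + b1·ISS + b2·TRISS. There is no coefficient for L, hence no odds ratio or risk difference between cohorts.
- As research question 1 requires: logit P(death by day 30) = b0 + bL·L + b1·severity. The answer is bL with its interval.

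**2. What the remaining tests guarantee.** Risk-adjusted multivariable models are on the list, so an adjusted contrast is possible. Their outcome, exposure and adjusters are not stated, and the unadjusted tests stand beside them as equal options.

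**3. Set against the question.** Aim of the study and Study design fix the contrast and say it is risk-adjusted. The statistical section neither puts that contrast in its one specified model nor requires adjustment elsewhere.

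**4. What an unadjusted comparison could do.** Assumed inputs: 800 patients, two equal cohorts, about 15% mortality, no true effect of level of care, mean ISS 3 points higher in one cohort, TRISS represented as a composite of ISS, physiology and age, 500 simulated trials.

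| Model | Mean log-odds ratio for level of care | Mean SE | Share with p < 0.05 |
|---|---|---|---|
| Level of care alone | 0.209 | 0.200 | 18.6% |
| Level of care + TRISS | 0.011 | 0.231 | 5.0% |
| Level of care + ISS + TRISS | 0.011 | 0.233 | 5.4% |

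The unadjusted odds ratio is exp(0.209) = 1.23 where the truth is 1.

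The documents do not give the case-mix difference, so a range is needed. The shift due to case mix is 0.209 − 0.011 = 0.198 for 3 points, or 0.066 per point. With b the shift and SE 0.20, the false-positive rate is approximately Φ(b/0.20 − 1.96) + Φ(−b/0.20 − 1.96). Scaling linearly:

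| Assumed ISS difference | Shift b | Odds ratio exp(b) | Approximate false-positive rate |
|---|---|---|---|
| 1 point | 0.066 | 1.07 | 6% |
| 2 points | 0.132 | 1.14 | 10% |
| 3 points | 0.198 | 1.22 | 17% |
| 5 points | 0.330 | 1.39 | 38% |

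**5. Whether ISS and TRISS together do harm.** In the same simulation, with a true log-odds ratio of 0.5, the level-of-care estimate was 0.496 with both scores (SE 0.220) and 0.496 with TRISS alone (SE 0.219). The variance inflation factor between the scores was about 1.5. The contrast is unaffected for practical purposes.

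**6. Whether the data can carry the corrected model.** Study population and sampling expects 800 analysed patients. The 15% in Study design is a benchmark ceiling, not a forecast, and is used here as an assumption. Expected deaths are 800 × 0.15 = 120, enough for a model with two or three terms. If all 800 fall into the two cohorts, the 95% half-width for a mortality difference is 1.96·√[0.15 × 0.85 × (1/n1 + 1/n2)]. That is 4.95 percentage points at 400/400 and 5.40 at 240/560. Clustering by hospital would usually widen this, and so would patients treated only in basic facilities, who belong to neither cohort.

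**7. Hospital effects.** Table 1 lists 2 maximum-care, 8 standard-care and 15 basic-care hospitals (2 + 8 + 15 = 25). Level of care is a property of the hospital, so L equals the sum of the two maximum-care hospital indicators. With a fixed effect for each hospital, bL is not identifiable.

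**The case against.** The best defence is that covariates ordinarily means adjusters. The contrast they adjust is stated in the aim and the design, and an article may leave the complete list of terms to an analysis plan that is not shown here. On that reading level of care is implied. The plan also calls itself mainly descriptive and does list risk-adjusted regression.

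Much of this stands. The exposure is unstated; it is not shown to be excluded. It does not remove the point, because the article chose to state the model and its covariates, and the stated model and test-selection rule do not match its own first question. The key term should not have to be guessed.

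A reader might infer four stronger things that the documents do not support:

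- That this is the only confirmatory model. The protocol never uses that word.
- That the study cannot answer research question 1. The listed risk-adjusted models could answer it, on an exploratory basis.
- That severity is wrongly counted twice because TRISS contains ISS. The documents do not say how TRISS is built, and overlap between adjusters does not bias the level-of-care effect (step 5).
- That leaving RISC out is an error. The article lists several scores as suitable for adjusted outcome, and using two of them is a choice.

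**Conclusion.** The point holds in limited form. The one specified model does not name level of care, and the rule for all other comparisons accepts unadjusted tests. Followed as written, the plan need not produce the risk-adjusted comparison of standard and maximum care.

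The textual conclusion needs no assumption. Its size depends on how far case mix differs between the cohorts, which the documents do not report. Under the assumptions above, false-positive rates for an unadjusted comparison run from about 6% at a 1-point ISS difference to about 38% at 5 points, against a nominal 5%. If the cohorts had the same case mix, the unadjusted test would keep its level, and the remaining fault would be the unnamed term. The direction of any bias cannot be told from the documents.

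**What to change.** In Biostatistical concept / statistical analysis:

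- Name level of care (maximum versus standard) as the exposure in the 30-day mortality logistic model.
- Adjust for a severity score already derived from the registry form: TRISS or RISC, with the other as a sensitivity analysis. Give the reason for the choice.
- Report the adjusted odds ratio and the adjusted risk difference, each with a 95% confidence interval that allows for clustering by hospital.
- Do not use fixed hospital effects, since level of care could then not be estimated. A random hospital intercept is one alternative. State plainly that only two maximum-care hospitals limit the precision of the contrast.
- Base the other between-cohort outcome comparisons on severity-adjusted regression suited to each outcome, and label unadjusted tests as descriptive.

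No new data are needed. The cost is slightly more analysis work, a handling rule for missing score components, and intervals that will probably be wider than an analysis ignoring hospitals would show.

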**Fig. 1 Fig1:**
[figure not shown]
Study design

The *prospective multicentre study* will (a) compare two cohorts of major trauma patients, those treated in maximum care facilities vs. those treated in standard care facilities, (b) compare results of the two cohorts with historical controls derived from the German Trauma Register DGU^®^ 2008 reference data and (c) compare results of the two cohorts with benchmarks including 5 outcome standards derived from the S3 guideline: risk adjusted morality (<15 %), door to CT-time (<20 min), ventilator free days (>22 days), ICU free days (>20 days), GOS (>80 % excellent and good).

The *qualitative part of the study* will (d) develop a service mapping tool (“blueprinting”) derived from quality management in the service industry in order to structure and visualize the care process for major trauma patients in the TNO, and (e) employ focus group discussions for identifying barriers and facilitators during the process, which can serve to explain why benchmarks are or are not met. This design allows for a comprehensive evaluation of TNO. In addition, the triangulation of methods provides for a profound understanding of the processes involved in acute major trauma care as well as the causal relationship between processes, structures and patient outcome. Whereas the quantitative study supplies data of patient outcome, and allows for comparisons between different health care standards plus the comparison of these results to benchmarks, the additional qualitative data provide an aid to interpretation and thus help in using the data for improvement of care processes and quality of care.

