### Study population and sampling

Patients will be recruited within the 25 hospitals that comprise TNO (Table 1). Inclusion criteria for the *prospective cohort study* are: major trauma ISS ≥ 16 (Injury Severity Score), treatment in any of the care facilities within the trauma network TNO, no age limitations. Exclusion criteria are ISS < 16, care outside TNO. Based on current register data it is expected that *n* = 1.100 patients will be assessed for eligibility and n = 800 be included and analyzed. For the *qualitative analysis* of barriers and facilitators, focus groups will be conducted with representatives of different professional groups involved in the TNO including emergency physicians, paramedics, dispatch centre staff, emergency room staff, trauma surgeons, rehabilitation staff and social workers. The focus group methodology can be transferred to other trauma networks and can be spread throughout Germany.

**Table 1 Tab1:** Trauma Network Eastern Bavaria / recruiting centres

Centre	Level of care
University Hospital Regensburg	Maximum Care Facility
Krankenhaus der Barmherzigen Brüder Regensburg	Maximum Care Facility
Klinikum Amberg	Standard Care Facility
Klinikum Eggenfelden	Standard Care Facility
Klinikum Deggendorf	Standard Care Facility
Klinikum Landshut-Achdorf	Standard Care Facility
Klinikum Neumarkt	Standard Care Facility
Klinikum Passau	Standard Care Facility
Klinikum Straubing	Standard Care Facility
Klinikum Weiden	Standard Care Facility
Krankenhaus Bogen	Basic Care Facility
Krankenhaus Burglengenfeld	Basic Care Facility
Krankenhaus Cham	Basic Care Facility
Krankenhaus Dingolfing	Basic Care Facility
Krankenhaus Freyung	Basic Care Facility
Krankenhaus Kelheim	Basic Care Facility
Krankenhaus Mallersdorf	Basic Care Facility
Krankenhaus Marktredwitz	Basic Care Facility
Krankenhaus St. Josef Regensburg	Basic Care Facility
Krankenhaus Schwandorf	Basic Care Facility
Krankenhaus Viechtach	Basic Care Facility
Krankenhaus Vilsbiburg	Basic Care Facility
Krankenhaus Vilshofen	Basic Care Facility
Krankenhaus Waldkirchen	Basic Care Facility
Krankenhaus Zwiesel	Basic Care Facility

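### Level of care is a hospital-level exposure (2 maximum-care versus 8 standard-care hospitals), but the named analyses make no allowance for hospital, so p values and confidence intervals for it will be too optimistic

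*Protocol article*

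**What the plan says.** The Study design section (text with Fig. 1) says the study will "compare two cohorts of major trauma patients, those treated in maximum care facilities vs. those treated in standard care facilities". Level of care is a property of the hospital, so all patients in one hospital share it.

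Under Study population and sampling, "Patients will be recruited within the 25 hospitals that comprise TNO", and it is expected that "n = 800 be included and analyzed". Table 1 classifies 2 hospitals as maximum care (the University Hospital Regensburg and "Krankenhaus der Barmherzigen Brüder Regensburg"), 8 as "Standard Care Facility" and 15 as basic care.

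Under Biostatistical concept / statistical analysis, the mortality model is stated: "A logistic regression will be performed with 30 day mortality as the dependent variable and the ISS and TRISS scores as covariates". Then: "A p value of < 0.05 will be considered statistically significant". For the rest, "All other statistical tests will be chosen according to the scale level of the variable and the number of variables used in the model", followed in brackets by the t-test, Mann–Whitney test, chi-squared test and risk-adjusted multivariable regression. The descriptive output is to include confidence intervals.

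The Aim of the study section hypothesises that outcomes in the two types of hospital are equal. The article nowhere mentions a hospital term, clustering, a multilevel model, robust standard errors or an ICC.

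**The concern.** In their standard form, the three named tests and an ordinary logistic regression treat patients as independent. Patients in the same hospital share staff, equipment and procedures, so their outcomes may be correlated even after adjustment for injury severity. When the exposure does not vary within a hospital, that correlation goes straight into the variance of the comparison. It weighs most heavily here on the maximum-care cohort, which consists of two clusters.

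Two things are at stake. A difference between levels of care could be declared significant when it reflects ordinary variation between hospitals. And because the sponsor expects equality, an interval that is too narrow around a small difference would look like firmer support for that hypothesis than the data give.

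A design limit comes on top. With both maximum-care hospitals in Regensburg, a level-of-care effect cannot be told apart from an effect of those two hospitals or that city. The Discussion itself describes the university hospital as among the most advanced of its kind, yet the abstract and the Discussion extend the results to most comparable parts of Germany.

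**Working it through.** The article has no power calculation, margin, ICC or patient split by level of care. The 800 is a recruitment forecast, so there is no figure of the plan's own to reproduce.

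**From the article:** 2 and 8 hospitals (Table 1; 2 + 8 + 15 = 25); 800 patients; alpha 0.05, taken as two-sided. The 15% mortality is the article's benchmark limit, used only as a working value.

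**Assumed:** all 800 patients fall in the two cohorts, split 400/400; hospitals within a level are of equal size (400/2 = 200 and 400/8 = 50); ICC 0.001 to 0.02; an unadjusted comparison of proportions.

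**Formulas**
- Design effect per cohort: DE = 1 + (m − 1) × ICC, with m = 200 or 50.
- Variance ratio R with equal cohorts: (DE_max + DE_std)/2.
- Actual type I error of the nominal 5% test: 2 × [1 − Φ(1.96/√R)].
- Half-width with independent patients: 1.96 × √[0.15 × 0.85 × (1/400 + 1/400)] = 1.96 × 0.02525 = 4.9 points. With clustering, multiply by √R.

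**Example, ICC 0.01:** DE_max = 1 + 199 × 0.01 = 2.99; DE_std = 1 + 49 × 0.01 = 1.49; R = 2.24; √R = 1.50. Type I error = 2 × [1 − Φ(1.31)] = 19.0%. Half-width 7.4 points.

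| ICC | DE_max | DE_std | R | Type I error | Half-width, normal (points) | Half-width, t on 8 df (points) |
|---|---|---|---|---|---|---|
| 0.001 | 1.20 | 1.05 | 1.12 | 6.5% | 5.2 | 6.2 |
| 0.005 | 2.00 | 1.25 | 1.62 | 12.4% | 6.3 | 7.4 |
| 0.01 | 2.99 | 1.49 | 2.24 | 19.0% | 7.4 | 8.7 |
| 0.02 | 4.98 | 1.98 | 3.48 | 29.3% | 9.2 | 10.9 |

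The 8 degrees of freedom are 10 hospitals minus 2 groups.

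**Checks.** A beta-binomial simulation of the unadjusted two-proportion test (40,000 runs per setting) rejected in 6.3%, 12.3%, 18.9% and 29.4% of runs. Splits of 300/500 and 500/300 change little: 11.9%, 18.3% and 28.2% at ICC 0.005, 0.01 and 0.02.

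**Direction of what is left out.** Basic-care patients among the 800 would shrink the cohorts and lower the inflation. Adjustment for ISS and TRISS would lower it as far as case mix drives the differences between hospitals. Unequal hospital sizes within a level would raise it.

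**The case against.** Several counter-arguments have weight.

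- **This is a condensed article.** Handling of hospital effects could sit in a full plan that is not shown, and multivariable regression is a class wide enough to include a mixed model. The mortality sentence does not even list level of care among its covariates. This stands in part. But the article does give its rule for choosing tests, and data structure is not in it. It also names tests that assume independence, and no later document can change the two-hospital cohort.
- **The plan is mainly descriptive,** and the remaining tests are described as explanatory. This softens the p value problem and lowers the severity. It does not help the confidence intervals, which are part of the descriptive output.
- **The aim is to evaluate this network, and all its hospitals are included.** If inference is confined to these hospitals, they are fixed and the computed inflation largely does not apply. This stands, and the fix must separate the two aims. It does not protect a conclusion about level of care, or the wider applicability that the article claims.
- **The remedy is not perfectly calibrated.** In simulation, a hospital-level t-test rejected in only 1.6% to 2.9% of runs at a nominal 5%. That conservatism is a real cost.

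A reader might infer that the effective sample is only about 10 hospitals. The documents do not support this: it would need an ICC near 1. Dividing 800 by the variance ratios 1.62, 2.24 and 3.48 gives about 490, 360 and 230 patients. A reader might also infer that the results are bound to be grossly optimistic. That does not follow either, since the ICC is unknown and at 0.001 the inflation is slight.

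**Conclusion.** The point holds in this form: the comparison is between hospital types, the named methods make no allowance for hospital, and for any conclusion about level of care the standard errors will be too small whenever outcomes are positively correlated within hospitals. The direction is clear, but the size is conditional. On the assumptions above it ranges from slight (type I error 6.5% at ICC 0.001) to serious (29% at 0.02, with the half-width nearly doubled). The ICC that matters is the one left after case-mix adjustment, which the article does not give.

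The two-hospital, one-city maximum-care cohort is a limit that analysis cannot remove; it has to be stated. This should be fixed. Given the primarily descriptive plan it falls short of a fatal flaw, and confidence in the size is medium.

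**What to change.** 1. In Biostatistical concept / statistical analysis, state that maximum versus standard comparisons account for hospital. Use either a hospital random intercept with small-sample degrees of freedom, or a hospital-level comparison of risk-adjusted rates. Do not rely on asymptotic sandwich errors, which are unreliable with two clusters in one cohort.
2. Report risk-adjusted rates for each hospital, for example in a funnel plot.
3. Separate the two aims: label any patient-level confidence interval as describing these hospitals only, and base statements about level of care on the analysis in item 1.
4. In the abstract and the Discussion, limit the generalisation by saying that, with two maximum-care hospitals in one city, a level-of-care effect cannot be separated from a hospital or city effect.

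**Cost:** changes of wording and analysis only. Referring and receiving hospital are already recorded (Quality assurance and safety), so no new data are needed. The price is wider, somewhat conservative intervals and a more modest claim.

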**Method/design:**

The design is based on a prospective multicenter cohort study comparing two cohorts of polytrauma patients: those treated in maximum care facilities and those treated in standard care facilities. Patient recruitment will take place in the 25 TNO clinics. It is estimated that *n* = 1.100 patients will be assessed for eligibility within a two-year period and *n* = 800 will be included into the study and analysed.

Main outcome measures include the TraumaRegisterQM form, which has been implemented in the clinical routine since 2009 and is filled in via a web-based data management system in participating hospitals on a mandatory basis. Furthermore, patient-reported outcome is assessed using the EQ-5D at 6, 12 and 24 months after trauma.

Comparisons will be drawn between the two cohorts. Further standards of comparisons are secondary data derived from German Trauma Registry as well as benchmarks from German S3 guideline on polytrauma.

The qualitative part of the study will be based on semi-standardized interviews and focus group discussions with health care providers within TNO. The goal of the qualitative analysis is to elucidate which facilitating and inhibiting forces influence cooperation and performance within the network.

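### The contrasts are named, but no outcome is designated to decide the comparable and outperforms hypotheses, and every test outside the mortality model keeps its own 0.05

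*Protocol article*

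**What the plan says.** All places are in the protocol article.

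- **Hypotheses (Aim of the study).** Outcome is expected to be the same in standard and maximum care when the hospitals work as a network. In addition, "we hypothesize that TNO outperforms German Trauma Register DGU^®^ 2008 reference data". The section goes on to say how the qualitative work will be used if the hypotheses hold and if they are contradicted, so a verdict on them is intended.
- **Main outcome (Abstract, Method/design).** "Main outcome measures include the TraumaRegisterQM form, which has been implemented in the clinical routine since 2009"; also, "patient-reported outcome is assessed using the EQ-5D at 6, 12 and 24 months after trauma". Data collection describes the form as having 40 items. No EQ-5D time point is preferred.
- **Contrasts (Study design).** Three are named: maximum versus standard care, the two cohorts versus 2008 register data, and a third, to "compare results of the two cohorts with benchmarks including 5 outcome standards derived from the S3 guideline". The five standards are mortality, door-to-CT time, ventilator-free days, ICU-free days and GOS, each with a numerical threshold.
- **Analysis (Biostatistical concept / statistical analysis).** "Statistical analyses of the prospective data will primarily dwell on descriptive statistics". One model is specified: "A logistic regression will be performed with 30 day mortality as the dependent variable and the ISS and TRISS scores as covariates". Then: "A p value of < 0.05 will be considered statistically significant". The remaining tests "will be performed in an explanatory manner, leaving alpha at < 0.05".

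**The concern.** These statements do not fit together. The hypotheses are worded for a decision, but the text does not say which result makes it. A data-collection form is not an endpoint. Mortality is set apart by having its own model, yet it is not called primary, and with only ISS and TRISS listed the model does not estimate the difference between care levels that the first hypothesis concerns.

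The outcomes can disagree. If mortality shows no significant difference while ICU-free days or EQ-5D at 12 months falls below 0.05, one reader can report the care levels as comparable and another as not comparable, both within the plan. The second hypothesis has the same gap, because no outcome or criterion is attached to outperforming the register. The Discussion directs the results to ministries, insurers and professional societies, so the choice of deciding result should not be open once the data are seen.

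**Working it through.** **Figures in the plan.** The relevant ones are the 0.05 level, applied per test, and n = 800 analysed of 1,100 assessed. The article gives no family-wise level, power, effect size or margin. The 800 is a register-based accrual forecast, so there is no derivation to reproduce.

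**Inputs for the false-positive check**
- Level per test: 0.05 (Biostatistical concept). The sidedness is not stated; two-sided is assumed.
- Number of tests: not fixed. Assumption A: the five standards in Study design are each tested between care levels, k = 5. Assumption B: EQ-5D at 6, 12 and 24 months is added, k = 5 + 3 = 8.
- Correlation between tests: not given, so a range is shown.

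**Independent tests.** P(at least one false positive) = 1 − 0.95^k.
- k = 5: 1 − 0.7738 = 22.6%
- k = 8: 1 − 0.6634 = 33.7%

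**Correlated tests.** Z_j = √ρ·U + √(1−ρ)·E_j, with U and E_j independent standard normal. The result is the simulated share of draws with any |Z_j| > 1.96.

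| k | ρ = 0 | ρ = 0.5 | ρ = 0.8 |
|---|---|---|---|
| 5 | 23% | 18% | 13% |
| 8 | 34% | 25% | 16% |

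The chance passes 50% only with 14 or more independent tests (k = 13: 48.7%; k = 14: 1 − 0.95^14 = 51.2%).

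**Can a non-significant mortality result show comparability?** Assume 15% mortality in both cohorts (the benchmark threshold, used only as an illustration) and 800 patients. The split between cohorts is not given. The half-width of the 95% confidence interval for the unadjusted difference is 1.96·√[0.15·0.85·(1/n₁ + 1/n₂)].
- 400 and 400: 1.96·√(0.1275·0.0050) = 4.9 to 5.0 points
- 160 and 640: 1.96·√(0.1275·0.0078125) = 6.2 points

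Power to detect 15% versus 20% is 46% at the even split and 29% at 20:80. As an illustration of scale, a 5-point non-inferiority margin at one-sided 0.025 and 80% power would need 1,602 patients in total. A true 5-point difference would therefore be missed more often than found, and a p value above 0.05 is weak evidence of equality.

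**The case against.** The case on the other side has substance.

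- **The plan does name contrasts and singles out an outcome.** Study design lists three contrasts and five benchmarks with thresholds, and the statistical section separates 30-day mortality from all other tests. A reader might infer that nothing at all is named. The text does not support that; what is missing is the designation of one outcome as deciding. The separation of mortality suggests a hierarchy but does not state one.
- **The analysis is declared mainly descriptive.** The word explanatory may be a slip for exploratory, and unadjusted testing is ordinary for exploratory work in an observational cohort. This stands as far as no claim is drawn from those tests. It does not remove the problem, because the Aim states hypotheses to be judged and the sentence retains a significance level.
- **The number of tests is an assumption.** The five standards are listed for comparison with thresholds, and the only explicit quality-of-life comparison is between men and women. For the register, the statistical section speaks of comparing descriptive results and specifies no tests. This stands: the percentages illustrate what the wording permits and are not error rates of written tests.
- **A chance finding is not shown to be likely.** A reader might infer that it is. At 13% to 34% the risk is clearly raised but below one half. Nor does the plan promise a family-wise 5%; its 0.05 is per test.
- **Alpha allocation may sit in an analysis plan or full protocol not shown.** That is fair for a testing order. However, the article is not silent: it states a main outcome, hypotheses and an alpha rule, and these conflict.

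**Conclusion.** The point holds in a limited form and should be corrected. No outcome is designated as deciding either hypothesis, the stated main outcome is a form plus EQ-5D at three times, the mortality model as written has no care-level term, and all other tests run at 0.05 each under an ambiguous label. Different outcomes can therefore support opposite conclusions from the same data.

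If eight outcomes were tested between care levels, the chance of at least one false-positive difference would be 16% to 34%, and with five outcomes 13% to 23%. These ranges rest on two-sided tests, the assumed counts and correlations from 0.8 down to 0.

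For the equality hypothesis, false positives count against what the investigators expect. The larger danger there is that a non-significant test is read as equality, since no margin is stated.

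**What to change.** 1. In the abstract and in Biostatistical concept / statistical analysis, replace the form as main outcome with risk-adjusted 30-day mortality, standard versus maximum care. Put the care-level term in the logistic model. Judge comparability from the confidence interval of that effect against a margin stated in advance, not from a p value above 0.05.
2. State that the claim to outperform the register rests on the same mortality outcome, for the network as a whole versus the 2008 data. Keep it as a separate question that does not depend on the result of step 1; the two are distinct research questions in the Aim.
3. Replace the sentence on the remaining tests with: exploratory manner, estimates with 95% confidence intervals, no confirmatory claim. Apply this to the other outcome standards, EQ-5D at all three times, the per-cohort register comparisons and the male-female comparison.

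The cost is wording, plus the work of choosing and justifying a margin; no new data or patients are needed. There are two downsides. A significant result on a non-primary outcome can no longer be reported as proof. And at n = 800 the mortality interval, about plus or minus 5 to 6 points at an assumed 15% mortality, may be too wide to show comparability. It is better to know that before the results are read.
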